**Cognitive function**	
The Montreal Cognitive Assessment (MoCA) will be used to explore changes in cognitive function. The MoCA is a well-known validated tool for assessing cognitive health and can be used for individuals on long-term dialysis	3 and 6 months
**Measures of safety**	
44-h intradialytic urine collection with paired blood samples to estimate residual kidney function	6 months
Serum beta-2 microglobulin, a validated surrogate for residual kidney function in individuals on long-term haemodialysis	Monthly
Serious adverse events (SAEs):	Monthly
• SAEs in totality (rate/years)	
• Vascular access complications that lead to SAEs (rate/years)	
• Dialysis prescription changes that lead to SAEs (rate/years)	
Clinical events:	Monthly
• Cardiovascular events (rate/years)	
• Cardiovascular mortality (rate/years)	
• Overall mortality (rate/years)	

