Individuals receiving haemodialysis within their home experience better quality of life and long-term clinical outcomes in comparison to in-centre haemodialysis [13, 14]. Home haemodialysis offers individuals flexibility regarding the length of dialysis sessions, time of day that treatment takes place and frequency of their treatment. Consequently, individuals can dialyse for longer, mimicking native kidney function to a greater extent compared to in-centre regimens, but with greater autonomy over the schedule. However, home haemodialysis is only utilised by approximately 2% of the UK KRT population [1]; there are considerable professional, patient and societal-related barriers to expanding home haemodialysis services [15, 16]. Alternative haemodialysis regimens are needed to address the dichotomy between in-centre and home haemodialysis therapies.

In-centre nocturnal haemodialysis (INHD) is an alternative regimen whereby individuals have the opportunity to dialyse overnight at a hospital-based or satellite dialysis unit, for 6 to 8 h per session. This increases the total weekly dialysis time to 18 to 24 h, a substantial increase compared to the typical 12 h of daytime in-centre haemodialysis, without impinging on dialysis-free time during the day. There is a growing body of evidence from observational data demonstrating that INHD is associated with improvements in HRQoL [17–20], dialysis adequacy [20–22], surrogates for cardiovascular health [23], survival [21, 24] and clinical parameters (e.g. anaemia and markers of renal bone disease) [17, 21–25]. It is probable that the reason for these observed benefits are due to both the increased dialysis dose and the overnight scheduling, which essentially increases the amount of usable dialysis-free time in comparison to usual in-centre daytime haemodialysis [26]. The extrapolation of these observational findings to the haemodialysis population are limited by significant sources of bias, in particular, selection bias and lack of randomisation, short follow-up period, small sample sizes and inadequate study power.

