### Aim and objectives {7}

The overall aim of the NightLife study is to test the clinical and cost-effectiveness of 6 months of thrice-weekly, extended-hours (6 to 8 h) INHD compared to standard care haemodialysis (thrice-weekly, 3.5 to 5 h of in-centre haemodialysis during the day) for adults requiring maintenance haemodialysis. This will be achieved with the following objectives:To determine the willingness and ability to recruit and randomise individuals to thrice-weekly, extended-hours INHD.To measure the effect of 6 months of extended-hours INHD compared with daytime haemodialysis on quality of life.To measure the effect of 6 months of extended-hours INHD compared with daytime haemodialysis on sleep, fatigue, dialysis recovery, cognitive function, clinical parameters and dialysis adequacy and safety (including residual kidney function and vascular access complications).To assess feasibility and acceptability of extended-hours INHD to individuals receiving long-term in-centre haemodialysis, their family and care givers, and staff, in order to identify contextual factors that influence the implementation of INHD.To evaluate the cost-effectiveness of 6 months of extended-hours INHD compared with daytime haemodialysis from a health and social care perspective.To understand and address issues that undermine recruitment and retention in the NightLife study.

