### Intervention description {11a}

Participants allocated to the intervention group will receive thrice-weekly, extended-hours (6 to 8 h) INHD for 6 months. The participants allocated to the control arm will continue with thrice-weekly, standard-hour (3.5 to 5 h) in-centre daytime haemodialysis. All other aspects of dialysis care will remain the same.

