### Participant timeline {13}

Overview of participant timeline and schedule of events is summarised in Fig. 1. The schedule of enrolment, randomisation, assessments and follow-up are summarised in Table 3.

**Table 3 Tab3:** The schedule of enrolment, randomisation, assessments and follow-up

Procedure	Screening	Baseline	1 month	2 months	3 months	4 months	5 months	6 months	3 years
Review eligibility criteria	X	X							
Written informed consent		X							
Demographic data and medical history		X							
Questionnaires: KDQoL, EQ-5D-5L, PSQI, SONG-HD, TTR		X	X		X			X	
MoCA		X			X			X	
Baseline health economics questionnaire		X							
Randomisation		X							
Intradialytic urine collection and paired blood samples*		X						X	
Serum beta-2 microglobulin*		X	X	X	X	X	X	X	
Resource use and expenditure questionnaire			X		X			X	
Routine clinical data^◊^ including adherence, dialysis adequacy, blood pressure and monthly blood results		X	X	X	X	X	X	X	
Capture of routine clinical data and resource usage (UKRR, SRR, HES, ONS, ISD)									X

*Blood samples drawn at the same time as routine clinical testing. ^◊^Routinely collected data on all dialysis units

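### Monthly serum beta-2 microglobulin is not a clean between-arm measure of residual kidney function when the arms differ in dialysis hours by design; the 6-month urine measure should carry that conclusion

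*Protocol article*

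**What the plan says.** Table 2 of the protocol article, under measures of safety, has two rows on residual kidney function. One is direct: "44-h intradialytic urine collection with paired blood samples to estimate residual kidney function", with follow-up at 6 months. The other is monthly: "Serum beta-2 microglobulin, a validated surrogate for residual kidney function in individuals on long-term haemodialysis". The schedule in Table 3 places the urine collection at baseline and month 6 only, and beta-2 microglobulin at baseline and every month from 1 to 6.

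The intervention is "thrice-weekly, extended-hours (6 to 8 h) INHD for 6 months" and the control is "thrice-weekly, standard-hour (3.5 to 5 h) in-centre daytime haemodialysis"; all other dialysis care is to stay the same (Intervention description {11a}). The background says of INHD: "This increases the total weekly dialysis time to 18 to 24 h", against a typical 12 h, and names the larger dialysis dose as one probable source of benefit.

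The objectives include "safety (including residual kidney function and vascular access complications", and the background reports that an earlier nocturnal trial found a faster decline of residual function in its intervention arm. The secondary-outcomes paragraph of section {20a} assigns repeatedly measured outcomes to a mixed linear model. All secondary analyses are adjusted for baseline value, dialysis unit and age.

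**The concern.** At steady state a serum level is generation divided by total clearance: renal, dialytic and any other route. It can stand in for the renal part only where the other parts are similar in the groups compared. Here the trial makes the dialytic part differ. The shift begins after randomisation, so adjusting for the baseline level does nothing about it, and unit and age do not measure it.

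The direction matters. More dialytic removal lowers the level on INHD, and a lower level read as residual function looks like preservation. That is the opposite of the harm that the background takes seriously. From month 1 to month 5 this marker is the only residual-function information in the schedule. The article labels both rows as measures of residual function and does not say which governs if they disagree.

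**Working it through.** **Dialysis hours (from the documents).** INHD: 3 × 6 = 18 h and 3 × 8 = 24 h a week, which reproduces the stated range. Control: 3 × 3.5 = 10.5 h to 3 × 5 = 15 h; the typical 12 h is 3 × 4 h. The ratio to typical is 18/12 = 1.5 to 24/12 = 2.

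**Assumed inputs (not in the documents).** Dialyser clearance of the marker Kd = 10 to 60 mL/min; non-renal clearance Kn = 1 to 3 mL/min; renal clearance Kr = 1 to 5 mL/min; distribution volume V = 10 L in a single pool; constant generation G, which cancels in every ratio below. Blood is assumed to be drawn before dialysis. The article says only that it is drawn with routine testing.

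**Check 1: time-averaged level.** Averaged over the week, C = G / (Kr + Kn + Kd × h/168). The extra hours offset a renal loss of Kd × (extra weekly hours)/168, for 12 h rising to 18 or 24 h:
- Kd 0: 0 mL/min
- Kd 10: 10 × 6/168 = 0.36 to 10 × 12/168 = 0.71 mL/min
- Kd 30: 1.07 to 2.14 mL/min
- Kd 60: 2.14 to 4.29 mL/min

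This is an upper picture, because it ignores the recovery of the level between sessions.

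**Check 2: pre-dialysis level.** During a session, V dC/dt = G − (Kr + Kn + Kd)C; between sessions the Kd term drops out. Sessions start at 48, 48 and 72 h intervals, run to a steady weekly cycle, with 6 or 8 h on INHD against 4 h on control.

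With Kr = 3 and Kn = 3, sampled after a two-day interval, the INHD level at unchanged residual function is 2% to 7% lower for Kd 10 to 60. That hides a renal loss of about 0.15 to 0.67 mL/min, which is 0.15/3 = 5% to 0.67/3 = 22% of the starting value. At Kd = 0 nothing is hidden.

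Over the whole assumed grid, the mean of the three weekly pre-dialysis levels is about 1% to 18% lower at unchanged residual function. The upper end is about 13% if blood is always drawn after the long interval and about 21% if it is always drawn after a two-day interval.

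**What a real loss would look like.** Kd = 30, Kn = 3, starting Kr = 3, sampled after a two-day interval. Entries are levels relative to control hours with Kr = 3:

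| Residual function | 4 h | 6 h | 8 h |
|---|---|---|---|
| Unchanged | 1.00 | 0.96 | 0.93 |
| Half lost | 1.24 | 1.17 | 1.11 |
| All lost | 1.62 | 1.47 | 1.37 |

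The loss still shows, but it is understated. Over the grid, using the weekly mean, complete loss from a starting Kr of 3 raises the level by about 37% to 142% on INHD hours and 54% to 180% on control hours. It leaves the level almost unchanged (ratio about 1.00 to 1.01) with starting Kr of 1, Kn of 1, 8-h sessions and Kd of 30 or more. Sampled after a two-day interval, that corner gives about 0.94 to 0.97.

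These figures are for participants who receive their allocated hours. If 25% of the INHD arm returns to daytime dialysis, as the sample-size section assumes, an arm-level difference of 7% shrinks to about 0.75 × 7% = 5%.

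**The urine row.** A clearance from timed urine and paired blood measures renal excretion directly, so dialytic removal of beta-2 microglobulin does not bias it. Its wording does need attention. No session lasts 44 h, so the collection cannot lie within one, yet Table 3 repeats the term: "Intradialytic urine collection and paired blood samples". If the period between sessions is meant, a 48-h cycle leaves 48 − 4 = 44 h after a 4-h session but 48 − 6 = 42 h to 48 − 8 = 40 h after an INHD session.

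**The case against.** The strongest reply is that the direct measure is already in the row above. Urine is collected at baseline and 6 months, so the comparison at the end of treatment does not depend on the serum marker. This stands, and it confines the problem to the monthly series. A reader might infer that the trial could miss a loss of residual function altogether; the documents do not support that.

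A second reply is that the effect may be small. This stands in part. A reader might use a simple ratio, 1/((1 − f) + f × k), with f the dialytic share of clearance and k its rise. With f = 0.5 and k = 1.25 this gives 0.89; with f = 0.9 and k = 2 it gives 0.53, a fall of 11% to 47%. Complete loss at f = 0.5 and k = 2 gives 1/(0.5 × 2) = 1.00, as if it were wholly hidden. That formula is time-averaged and leaves out non-renal clearance, and nothing in the documents supports those shares. On pre-dialysis levels the fall is smaller, and complete loss is hidden only in the corner shown above.

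A third reply is that the article nowhere says an arm difference in the marker will be read as a difference in residual function, and that interpretation belongs in the analysis plan. It is true that no such sentence is written. But the article does call the marker a surrogate for residual function, lists it as a safety outcome and fixes the adjustment set, and the plain reading of the resulting treatment estimate misleads. That is more than missing detail.

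Last, whether the cited validation covers groups with different session lengths cannot be checked from the documents, and they give no membrane or clearance. So the direction rests on one assumption: that dialysis removes some of the marker.

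**Conclusion.** The point holds for the monthly series. Given any dialyser clearance above zero, the between-arm comparison of serum beta-2 microglobulin is biased towards apparent preservation of residual function on INHD, and the planned adjustment cannot correct this. The illustrative size is a pre-dialysis level about 1% to 18% lower at unchanged residual function, under the assumed clearances above. It weakens the signal of a loss and seldom abolishes it.

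The consequence is limited but real. Residual function is a named safety objective, the bias runs towards reassurance, and the marker is the only information on it at months 1 to 5. The 6-month urine comparison remains sound on this count, although participants who leave before month 6 will not contribute to it. The primary outcome is untouched.

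**What to change.** - State that the between-arm safety conclusion on residual kidney function rests on the urine-based measure at 6 months.
- Describe the between-arm beta-2 microglobulin result as reflecting total clearance, dialytic plus renal, and say that a lower level on INHD will not be taken as evidence that residual function is preserved.
- Reconcile the 44-h intradialytic wording in Table 2, and the matching term in Table 3, with the session lengths in both arms, since the conclusion would then rest on that collection.

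The cost is a few sentences; samples, visits and models stay as they are. The small downside is that no unconfounded comparison of residual function between arms is available before month 6. Moving the row to another heading would change no result. Restricting the marker to change within each arm would give up the randomised comparison, so neither is needed.

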**Impact on clinical parameters**	
Blood results: haemoglobin, ferritin, transferrin saturation, calcium, potassium, phosphate, parathyroid hormone	Monthly
Dialysis adequacy assessed via urea reduction ratio and Kt/V (determined from pre-dialysis urea, post-dialysis urea, post-dialysis weight and ultrafiltration volume	Monthly
Pre-dialysis blood pressure	Monthly
Medication prescription: antihypertensive agents, phosphate binders, potassium binders, erythropoietin, iron supplementation	6 months
**Adherence to allocated study arm**	
Number of missed dialysis sessions	Monthly
Minutes per dialysis session	Monthly
Number of dialysis sessions not achieving time criteria	Monthly
Number of temporary changes from treatment allocation (i.e. participant allocated to intervention dialysing during the day	Monthly
**Cost-effectiveness**	
Resource use and expenditure questionnaire	1, 3 and 6 months

### Participant timeline {13}

Overview of participant timeline and schedule of events is summarised in Fig. 1. The schedule of enrolment, randomisation, assessments and follow-up are summarised in Table 3.

**Table 3 Tab3:** The schedule of enrolment, randomisation, assessments and follow-up

Procedure	Screening	Baseline	1 month	2 months	3 months	4 months	5 months	6 months	3 years
Review eligibility criteria	X	X							
Written informed consent		X							
Demographic data and medical history		X							
Questionnaires: KDQoL, EQ-5D-5L, PSQI, SONG-HD, TTR		X	X		X			X	
MoCA		X			X			X	
Baseline health economics questionnaire		X							
Randomisation		X							
Intradialytic urine collection and paired blood samples*		X						X	
Serum beta-2 microglobulin*		X	X	X	X	X	X	X	
Resource use and expenditure questionnaire			X		X			X	
Routine clinical data^◊^ including adherence, dialysis adequacy, blood pressure and monthly blood results		X	X	X	X	X	X	X	
Capture of routine clinical data and resource usage (UKRR, SRR, HES, ONS, ISD)									X

*Blood samples drawn at the same time as routine clinical testing. ^◊^Routinely collected data on all dialysis units

### Sample size {14}

The recruitment target is 350 participants; 150 to the control arm and 200 to the intervention arm. This recruitment target consists of both the sample size required to achieve study power and considerations for participant drop-out.

The study is powered to detect a standardised difference of 0.26 in the KDQoL total score between groups over 6 months, adjusting for baseline KDQoL total score with correlation coefficient of 0.78. To achieve 90% power and a type I error rate of 5%, 252 participants are required. Assuming an overall attrition rate of 15%, and 25% non-adherence with INHD in the intervention group, the targeted number of randomisations is 350 (150 to control arm, 200 to intervention arm). This will ensure adequate power for both the intention to treat and per-protocol analyses.

Recruitment will be reviewed by the independent Data Safety and Monitoring Committee to ensure the study remains adequately powered with respect to participant retention and permanent treatment arm crossover. Furthermore, as additional publications reporting the KDQoL-36 short form become available [37], the assumptions regarding the correlation coefficient between measurements during follow-up will be reviewed to ensure maximal study power is achieved.

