### Assignment of interventions: allocation

#### Sequence generation {16a}

Participants will be randomised after informed consent has been provided and baseline questionnaire data collected. Allocation will be weighted towards to the intervention (1:1.33, control:intervention) to account for the assumed 25% conversion back to in-centre daytime haemodialysis from the intervention group within the first 2 weeks (see above). Randomisation will be stratified by haemodialysis unit and age (< 65 years, ≥ 65 years) and managed by the Leicester Clinical Trials Unit.

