## Statistical methods

### Statistical methods for primary and secondary outcomes {20a}

#### Primary outcomes

The primary outcome will compare the KDQoL composite score over 6 months between the intervention and control. The primary outcome analysis will be conducted using a modified intention to treat with participants with at least one post baseline measurement of KDQoL analysed in the groups to which they were randomly allocated, regardless of haemodialysis schedule they actually received. The KDQoL total score over 6 months (i.e. 1, 3 and 6 months) will be compared between the treatment arms using a repeated measures mixed linear regression model with participant as a random effect to account for repeated measures over time. The model will be adjusted for a treatment group, minimisation factors (haemodialysis unit and age) with haemodialysis unit as a random effect and baseline KDQoL total score. Treatment comparison estimates will be presented as adjusted mean difference and 95% confidence intervals.

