### Methods for additional analyses (e.g. subgroup analyses) {20b}

There is increasing demand by clinicians and patients for ‘per-protocol’ analyses which quantify the effect of being randomised to, receiving and continuing a treatment [44]. A secondary, complier average causal effect (CACE) analysis will be conducted to understand the efficacy of extended-hours INHD in those that receive it as planned.

Clinical experience suggests that the development of new conditions which cause instability of the patient whilst they are on haemodialysis may mean that patients allocated to INHD will have to return to usual care during the day. The effect of such switching on the treatment effect found will be assessed.

Subgroup analyses will be limited to the same variables used as minimisation variables. Tests for statistical heterogeneity (e.g. by including treatment group by subgroup interaction parameter in the regression model) will be performed prior to any examination of effect estimate within subgroups.

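### The inflation to 350 restores the number of adherers but not the diluted ITT effect, so the claim of adequate power for both ITT and per-protocol analyses is unsupported until the plan says which effect 0.26 is

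*Protocol article*

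**What the plan says.** Sample size {14} sets the target: "The study is powered to detect a standardised difference of 0.26 in the KDQoL total score between groups over 6 months". The calculation takes credit for the baseline score as a covariate, at an assumed correlation of 0.78. It continues: "To achieve 90% power and a type I error rate of 5%, 252 participants are required". The step to 350 randomised (150 control, 200 intervention) follows: "Assuming an overall attrition rate of 15%, and 25% non-adherence with INHD in the intervention group". The paragraph closes with the claim at issue: "This will ensure adequate power for both the intention to treat and per-protocol analyses".

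Three other places bear on it:

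- Sequence generation {16a}: "Allocation will be weighted towards to the intervention (1:1.33, control:intervention) to account for the assumed 25% conversion back to in-centre daytime haemodialysis". The same sentence places this conversion in the first 2 weeks.
- Statistical methods, Primary outcomes: a modified ITT analysis by randomised group, "regardless of haemodialysis schedule they actually received", using KDQoL total score at months 1, 3 and 6.
- Methods for additional analyses {20b}: after noting the demand for per-protocol analyses, the plan says that a secondary "complier average causal effect (CACE) analysis will be conducted to understand the efficacy of extended-hours INHD" in those who receive it as planned.

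**The concern.** Dividing the intervention arm by 0.75 is the right allowance if non-adherers are removed from the comparison. Here they are not removed. Someone who returns to daytime dialysis within 2 weeks has done so before the first follow-up KDQoL at month 1, yet stays in the INHD arm for the primary analysis. If such people gain nothing, the between-group difference shrinks to 0.75 of the adherer effect, and the required number rises by 1/0.75² = 1.78. Enlarging one arm by 1/0.75 does not make that up. CACE does not escape either: it rescales the ITT difference by the proportion adhering, and its standard error grows in step.

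Two things are at stake. A null primary result could be read as coming from a trial with about 90% power for the targeted effect when the delivered power may be lower. Also, Sample size {14} asks the monitoring committee to watch power against permanent crossover. On the head-count logic, 25% crossover looks already paid for, whereas crossover erodes the primary comparison directly.

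**Working it through.** **Inputs.** From Sample size {14}: standardised difference 0.26; baseline correlation 0.78; power 90%; type I error 5% (taken as two-sided, since the article does not say); 252 evaluable; 150 and 200 randomised; 15% attrition; 25% non-adherence. From Sequence generation {16a}: ratio 1:1.33, reversion within 2 weeks. Not in the article: the share of benefit that reverters keep (varied from 0 to 100%) and the correlations between follow-up visits (varied from 0.78 to 1.0).

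**1. Reproduce 252.** The ANCOVA variance factor is 1 − 0.78² = 0.3916. With equal arms, n per arm = 2 × (1.96 + 1.2816)² × 0.3916 / 0.26² = 121.7, so 244 in total. At 1:1.33 the normal formula gives 107 + 143 = 250, and a noncentral-t version gives 108 + 144 = 252 (power 0.902). The figure reproduces.

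**2. Reproduce 350.** 126/0.85 = 148.2 controls and 126/(0.85 × 0.75) = 197.6 intervention, total 346, rounded up to 150 + 200. Read forwards: 150 × 0.85 = 127.5 controls, and 200 × 0.85 × 0.75 = 127.5 adherent INHD participants. The inflation restores the number of adherers.

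**3. The comparison that this sizes.** Adherers against controls, 127.5 v 127.5: SE = √(0.3916 × 2/127.5) = 0.0784; power = Φ(0.26/0.0784 − 1.96) = 91%. This comparison is not in the plan.

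**4. The planned ITT comparison.** Evaluable: 150 × 0.85 = 127.5 v 200 × 0.85 = 170. SE = √(0.3916 × (1/127.5 + 1/170)) = 0.0733.

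| Meaning of 0.26 | Benefit kept by reverters | ITT effect | ITT power |
|---|---|---|---|
| ITT difference | any | 0.26 | 94% |
| Effect in adherers | none | 0.75 × 0.26 = 0.195 | 76% |
| Effect in adherers | 25% | 0.211 | 82% |
| Effect in adherers | 50% | 0.2275 | 87% |
| Effect in adherers | 75% | 0.244 | 91% |
| Effect in adherers | 100% | 0.26 | 94% |

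For the second row: Φ(0.195/0.0733 − 1.96) = 0.758.

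**5. CACE.** A 20,000-run simulation of the second row (128 v 170, 75% adherent) gave ITT 75.4%, CACE 76.0% and adherers-only 91.4%. CACE tracks ITT, not the adherers-only comparison.

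**6. What the extra intervention participants buy.** At an effect of 0.195, 127.5 v 127.5 gives about 70% and 127.5 v 170 about 76%. The weighting offsets dilution in part.

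**7. Three-visit model.** Averaging months 1, 3 and 6, with correlation 0.78 between baseline and each visit and ρ between follow-up visits, the variance factor is (1 + 2ρ)/3 − 0.78². For a constant diluted effect of 0.195:

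| ρ | 0.78 | 0.85 | 0.90 | 0.95 | 1.0 |
|---|---|---|---|---|---|
| Power | 92% | 87% | 83% | 79% | 76% |

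**8. Detectable difference at 90% power.** (1.96 + 1.2816) × 0.0733 = 0.238 for ITT. If reverters gain nothing, this corresponds to 0.238/0.75 = 0.317 in adherers.

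**The case against.** A reader might infer that the trial has 76% power rather than 90%, and that the sentence is simply false. The documents do not support that. The 76% needs 0.26 to be the adherer effect and reverters to gain nothing, and the article states neither. Sample size {14} describes 0.26 as a difference between groups, and Outcomes {12} ties it to a 5-point difference judged clinically important, not to an estimate in people who stay on INHD. Read literally as the ITT target, it gives about 94% power, and the CACE test, which tracks ITT, does equally well. The article attaches 90% only to the 252; for the two analyses it says no more than adequate. Also, 76% is the lower end for the planned repeated-measures model when the diluted effect is constant. All of this stands.

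It does not rescue the text. If 0.26 is the ITT difference, ITT needs only 252/0.85, about 296 randomised, with no allowance for non-adherence. If reverters gain nothing, the adherer effect is then 0.26/0.75 = 0.347, and even an adherers-only comparison has about 99% power. The 25% inflation would serve no analysis. It makes sense only if 0.26 is the effect in adherers, and then it does not protect ITT or CACE.

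Two further points are fair. The weighting does account for conversion in the sense of equalising numbers on treatment. And the article commits to reviewing power against crossover, and the correlation assumption as new data appear; that is a partial safeguard, but it does not settle which effect is being powered.

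**Conclusion.** The concern holds in a limited form. The arithmetic behind 252 and 350 reproduces; the statement drawn from it is unsupported rather than shown to be false. One value of 0.26 cannot be both the ITT difference and the adherer effect unless reverters benefit fully, and the inflation sizes a comparison that the plan does not make.

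By the plan's single-time-point formula, ITT power is about 94% on the ITT reading. On the adherer reading with no benefit in reverters, it is about 76% for both ITT and CACE. Reversion within 2 weeks makes little retained benefit plausible, but the article does not assume it; ITT power is 82% or 87% if 25% or 50% is kept. In those cases CACE would also no longer equal the adherer effect, because it credits the whole ITT difference to adherers. The 76% to 92% range for the three-visit model assumes a constant diluted effect of 0.195 and correlation 0.78 between baseline and each visit. An effect that builds up over time is not quantified here, since the article gives no profile for it.

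**What to change.** In Sample size {14}:

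- State whether 0.26 is the difference between randomised groups or the effect in those who stay on INHD.
- Replace the closing power sentence with the ITT and CACE power delivered under 15% attrition and 25% early reversion. Show the assumed benefit kept by reverters and the assumed correlations between visits.
- Give the ITT difference detectable at 90% power: about 0.24 by the plan's formula, equivalent to about 0.32 in adherers if reverters gain nothing.

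In Sequence generation {16a}, say that the 1:1.33 weighting equalises the numbers on treatment and only partly offsets dilution of the ITT effect.

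The cost is wording and, depending on which effect 0.26 turns out to be, a less favourable stated power. No extra participants are needed for this correction.
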